## Methods

### Study design

This study will involve a longitudinal cohort design using de-identified, electronic medical records extracted for the period 1 January 2009 to 31 December 2017.

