**Fig. 1 Fig1:**
[figure not shown]
Method for calculating the prevalence of HIV viraemia among diagnosed and undiagnosed gay and bisexual men

#### Outcome 2

HIV incidence will be calculated using repeat testing among the negative cohort, [18] which will consider patients with two or more HIV tests for whom the first test was negative. We expect that more than 80% of gay and bisexual men will have at least two tests over the study period. An incident infection will be defined as an HIV diagnosis following a negative test and time at risk will be calculated as the time between each patient’s first and last test or a patient’s first test and HIV diagnosis. The number of incident infections will be divided by the person time (in years) at risk.

#### Outcome 3

Data from the positive cohort will also be used to calculate the incidence of ART initiation (i.e., the point at which ART is initiated) with the follow-up period defined as the time after HIV diagnosis (person years of infection). This variable will be restricted only to men diagnosed with HIV during the study period.

#### Outcome 4

Data from the negative cohort will be used to calculate the incidence of repeat diagnostic HIV testing. The incident event is defined as the point at which a patient achieves a second HIV test within six weeks to 12 months of a previous test, with follow-up time defined as the period between a patient’s first HIV test and last clinical encounter. Follow-up time will cease if a patient has no recorded service event of any kind within a two year period but will resume at the point of future service events (i.e., reengages with a participating service). Follow-up will also cease if a patient is diagnosed with HIV.

#### Outcome 5

Among the positive cohort, the incidence of viral suppression will be calculated. Viral suppression is defined as two consecutive viral load tests of <200 RNA copies/mm^3^ separated by at least three months; the first test will be taken as the point of suppression for calculating time. This variable will only be calculated among patients with no history of previous treatment and will exclude those for whom there is no or only one viral load test result. We will conduct a sensitivity analysis with a higher viral load threshold of <1000 RNA copies/mm^3^.

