The third analysis will determine incidence and predictors of repeat HIV testing (Secondary Aim 2). To calculate annual estimates we will allocate follow-up time and the incident of repeat testing (i.e., the point at which a second test is achieved) to the calendar year in which it occurs. With this approach it is possible that a patient might achieve multiple incidents of repeat testing in one calendar year. In addition to evaluating changes in the incidence of repeat HIV testing over time, this analysis will employ a regression analysis to identify demographic, behavioural and clinical factors associated with repeat testing incidence among gay and bisexual men in the negative cohort.

The fourth analysis will estimate the incidence of viral suppression among those newly diagnosed and predictors of incidence of viral suppression among the positive cohort (Secondary Aim 3). This analysis will employ Cox proportional hazards regression. Further, we will estimate the median time from diagnosis to first viral suppression by calendar year among those who are diagnosed during the study period, stratified by CD4 cell count at diagnosis. For this analysis and all others, statistical significance will be set at *p* < 0.05.

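### Viral suppression is back-dated to a test that needs confirmation at least three months later, data stop on 31 December 2017, and Outcome 5 states no end of follow-up that removes the time when events cannot be seen

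*Protocol article*

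**What the plan says.** Protocol article, Methods, Study outcomes, Outcome 5: the event is a pair of successive viral loads below 200, "separated by at least three months; the first test will be taken as the point of suppression for calculating time". Men with earlier treatment are left out, and the analysis "will exclude those for whom there is no or only one viral load test result". On follow-up there is only the general statement "Among the positive cohort, the incidence of viral suppression will be calculated"; no end of follow-up or censoring date is given. A sensitivity analysis raises the threshold to 1000 but does not mention changing the confirmation rule.

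Study design: the study uses "de-identified, electronic medical records extracted for the period 1 January 2009 to 31 December 2017".

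Other outcomes do define the end of time at risk. Outcome 2 stops at the last test or at HIV diagnosis. Outcome 4 stops at the last clinical encounter, with a rule for two-year gaps in service use and a stop at diagnosis.

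Data analyses, fourth analysis: Cox regression, and the plan to "estimate the median time from diagnosis to first viral suppression by calendar year" among men diagnosed in the study period. Sample size: 80% power is claimed for a 15% rise in the annual incidence of suppression (HR 1.15).

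**The concern.** Whether a first low result counts depends on a second result at least three months later, but the event takes the earlier date. Near the end of data the second result cannot exist. For the last three months of 2017 no event is possible, and for a longer stretch only men with closely spaced tests can contribute one. If those months count as time at risk, the 2017 rate falls for a purely mechanical reason.

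2017 is the final year of the period that the protocol calls full implementation of treatment as prevention. A real improvement in suppression could be masked there, or a fall reported that did not happen. Applying the 1000-copy threshold with the same confirmation rule would not reveal the problem.

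**Working it through.** **The plan's own yardstick.** The Sample size section gives 420 diagnoses a year, 90% treated, so 420 x 0.90 = 378 events a year. Read as one year against the next (756 events), Schoenfeld power at HR 1.15 is Φ(√(756/4) x ln 1.15 - 1.96) = Φ(1.921 - 1.960) = 48.5%, not the stated 80%. Two three-year pools (2268 events) give 91%. The point below does not depend on this; HR 1.15 serves only as a measure of the change sought.

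**The blind window.** 31 December 2017 minus three months is 30 September 2017. This needs no assumption.

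**Size in 2017.** Let g be the mean gap between viral loads in years (assumed; not in the article). Take a constant true rate and a steady number at risk.
- Events kept in 2017: about 1 - g, because a first test in the last g of the year has no confirming test.
- Follow-up to 31 December 2017: time at risk 1, so the rate ratio is about 1 - g.
- Censoring at the last viral load: this test lies on average g/2 before data end, so the ratio is about (1 - g)/(1 - g/2).
- Censoring at the second-last viral load: on average 1.5g before data end, so the ratio is about (1 - g)/(1 - 1.5g).

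The approximations were set against a simulation of 420 diagnoses a year over 2009-2017 with a constant hazard and a median of 0.5, 1 or 2 years to suppression. Men with fewer than two viral loads were excluded. Each cell gives the approximation, then the simulated 2017/2016 rate ratio; the true value is 1.00.

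| Assumed gap | g | To data end | Last viral load | Second-last viral load |
|---|---|---|---|---|
| about 3 months | 0.255 | 0.745; 0.72-0.75 | 0.854; 0.82-0.86 | 1.21; 1.17-1.22 |
| 3-5 months | 0.335 | 0.665; 0.65-0.68 | 0.799; 0.79-0.82 | 1.34; 1.32-1.37 |
| 5-7 months | 0.500 | 0.500; 0.47-0.51 | 0.667; 0.63-0.68 | 2.00; 1.94-2.03 |

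Both usual rules bias 2017 downward. Censoring at the second-last test overcorrects. Excluding men with fewer than two viral loads does not cure it.

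**Pooled 2015-2017.** One year in three is affected, so the ratio to the end of data is about 1 - g/3. For gaps of 3.0-3.6 months (g = 0.275) this is 0.908, simulated 0.89-0.90. For 3-6 months (g = 0.375) it is 0.875, simulated 0.85-0.86. Across gaps up to 5-7 months, the simulated ratio of 2015-2017 to 2012-2014 was 0.82-0.92 to data end and 0.90-0.96 with last-test censoring.

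**Time to suppression.** In one run (true median 12 months, gaps 3.0-3.6 months, follow-up to data end), the median for men diagnosed in 2016 rose from 1.14 to 1.26 years. For men diagnosed in 2017 it was not reached; short follow-up alone contributes to that.

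**Candidate repairs.** Closing follow-up three months early gives about (1 - g)/0.75 = 0.99, 0.89 and 0.67 for the three gaps (simulated 0.96-1.00, 0.87-0.91, 0.63-0.67), so three months is enough only with three-monthly tests. Closing on 30 June 2017 gives 1.00 when all gaps are within six months. With gaps spread evenly over 3-9 months, first tests in April-June 2017 are confirmed by data end about 75% of the time and those in January-March always, so the ratio is about (0.75 + 1)/2 = 0.875 (simulated 0.85-0.90). Extracting later viral loads for confirmation gives about 1.00 throughout.

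**The case against.** The strongest reply is that a censoring rule for a secondary outcome is detail that a condensed article may leave to a fuller document, and that Outcome 5 never says the unobservable time is counted. That stands: a reader might infer that the protocol keeps those months in the denominator, but the article neither keeps nor removes them, so the low 2017 rate is conditional. The reply does not dispose of the point. The event definition, the back-dating and the data end are all fixed in the article, and both customary censoring rules give a biased 2017 rate with them.

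Other stronger readings also fail:
- That the 2017 median time would show a fall. Lost events lengthen the median or leave it unreached.
- That the bias always exceeds the 15% change sought. The 2017 figure with last-test censoring starts at about 14%, and the pooled 2015-2017 figure is 10-15% with 3-6 monthly tests and follow-up to data end. The Sample size section itself foresees pooling and trend tests.
- That closing on 30 June 2017 always suffices. It does so only if confirmation gaps stay within about six months.

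It is also fair that the fourth analysis specifies Cox regression and medians, and that allocation of events to calendar years is spelled out only for repeat testing. The rate calculations correspond to the annual incidence named in the Sample size section; the bias in a Cox coefficient was not computed.

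**Conclusion.** The point holds in a conditional form. It follows from the stated rules alone that a first low viral load after about 30 September 2017 cannot count, and Outcome 5 gives no follow-up end that takes out this time. With no true change, the 2017 rate would be about 25-50% too low with follow-up to the end of data and about 14-35% too low with censoring at the last viral load. These sizes assume a constant hazard and mean test gaps of roughly three to six months. For 2015-2017 pooled, the shortfall to the end of data is about 10-15% with 3-6 monthly tests, more with wider gaps and less with last-test censoring. The direction opposes the increase sought under Secondary Aim 3. Years before 2017 are largely unaffected, and the primary aim, which uses the prevalence of viraemia, is untouched. The plan should be changed, but the secondary aim remains feasible.

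**What to change.** Add to Outcome 5 a fixed date before 31 December 2017 on which event follow-up for suppression closes, and state that later viral loads serve only to confirm first low results on or before that date. Set the date from the observed interval between viral loads; 30 June 2017 is enough if nearly all confirmation gaps are within six months. Alternatively, extract viral loads into 2018 for confirmation only, which keeps all of 2017 as event time. Apply the same rule to the 1000-copy sensitivity analysis and to the medians by calendar year. Do not censor each man at his own second-last test.

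The cost is one or two sentences, plus either six months or more of 2017 lost as event time for this secondary aim or a somewhat longer run of the routine electronic extraction.

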### Participants

Using de-identified data extracted from ACCESS sites, two patient cohorts of gay and bisexual men will be established: one comprising HIV positive men (‘positive cohort’) and the other HIV negative men (‘negative cohort’). The positive cohort will consist of approximately 13,000 HIV positive gay and bisexual men (approximately 90% of all gay and bisexual men with HIV in both states) and the negative cohort will consist of at least 40,000 HIV negative gay and bisexual men (approximately half of the population).

Both cohorts will be limited to men aged 16 years and older for whom there is at least once record indicating a history of sexual contact with other men. Indicators of same sex contact can be behavioural (i.e., self-reporting same sex partners), identity-based (i.e., recorded sexual orientation as gay or bisexual), or procedural (i.e., collection of an anal swab for STI testing). The positive cohort will include patients recorded as HIV positive or those who receive an HIV diagnosis during the study period. The negative cohort will include patients whose first record of HIV testing during the study period is negative. If during the course of the study a person is diagnosed with HIV, they will be reclassified to the positive cohort. Follow-up during the study period will be based on records from the participating services as well as the pathology conducted by participating laboratories.

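### Predictor model for viral suppression: no viraemia-at-entry condition and no time origin for men diagnosed before the study period, so unrecorded earlier treatment can appear as incident suppression

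*Protocol article*

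**What the plan says.** Under Study outcomes, Outcome 5 sets the event: "Viral suppression is defined as two consecutive viral load tests of <200 RNA copies/mm^3^ separated by at least three months". It also sets the event date: "the first test will be taken as the point of suppression for calculating time". There are two conditions for inclusion. One concerns treatment: "This variable will only be calculated among patients with no history of previous treatment". The other concerns the number of tests; the outcome "will exclude those for whom there is no or only one viral load test result". Neither concerns the value of the first viral load.

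The source population is described under Participants: "The positive cohort will include patients recorded as HIV positive or those who receive an HIV diagnosis during the study period". Men who were HIV positive before 2009 are therefore in it.

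Data analyses uses two populations for this outcome: "The fourth analysis will estimate the incidence of viral suppression among those newly diagnosed and predictors of incidence of viral suppression among the positive cohort". The only time origin given is for the descriptive estimate: "we will estimate the median time from diagnosis to first viral suppression by calendar year among those who are diagnosed during the study period". Study design limits extraction to 1 January 2009 to 31 December 2017.

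**The concern.** An incidence analysis needs people who are at risk when follow-up begins. For viral suppression that means not yet suppressed. Outcome 5 has no such condition. A man whose first two in-study results are both below 200 meets the event definition without ever having been seen with an unsuppressed viral load.

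For earlier-diagnosed men the only protection is the treatment-history exclusion, and it works only if earlier treatment is on record. Treatment given before 2009, overseas or at a non-participating service may not be.

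Secondary Aim 3 is partly about predictors. False events would fall among men with long-standing infection and incomplete records, not at random across the cohort. Hazard ratios for covariates related to earlier diagnosis or to transfer of care could then partly describe who arrived already treated.

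**Working it through.** No figure in the article depends on this definition, so there is nothing to reproduce. The check sets the sections side by side and then sizes the possible effect.

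**How the outcomes secure an at-risk state**
- Outcome 2 (HIV incidence): the first test must be negative.
- Outcome 3 (ART initiation): only men diagnosed in the study period.
- Outcome 5 (suppression): neither a starting viral load condition nor a diagnosis-period restriction. Data analyses restricts the incidence and median-time estimates to new diagnoses, but not the Cox predictor model.

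**Why treatment history may be incomplete.** The Cohorts section aims to capture at least 95% of viral load tests through laboratories, while clinical records come from 39 + 10 + 6 + 4 = 59 selected services. A viral load can thus be captured for a man whose treatment was managed elsewhere. Data sources describes probabilistic linkage, so a missed link can also separate viral loads from treatment records. That absence of history will often mean absence of a record is an inference; the article does not say how it is established.

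**Inputs for the size**
- Positive cohort about 13,000 (Participants), taken to include the new diagnoses.
- New diagnoses: 420 a year after a 30% reduction (Sample size), hence 420 / 0.70 = 600 before it. Each is applied to all 9 years as a bound.
- ART coverage 73% (Background, a 2014 figure), applied at entry as an assumption.
- 90% of new diagnoses start treatment (Sample size).
- Share of treated men with no treatment record: not given; 5-10% assumed.
- All treated men taken as suppressed, and all untreated earlier-diagnosed men taken to reach suppression during the study (both assumptions).

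**Low end (600 a year, 5% loss)**
- Earlier-diagnosed men: 13,000 - 9 × 600 = 7,600
- Treated: 7,600 × 0.73 = 5,548; false events: 5,548 × 0.05 = 277
- Genuine events: new diagnoses 0.9 × 600 × 9 = 4,860; untreated earlier-diagnosed men 7,600 × 0.27 = 2,052; total 6,912
- Added: 277 / 6,912 = 4%

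**High end (420 a year, 10% loss)**
- Earlier-diagnosed men: 13,000 - 9 × 420 = 9,220
- Treated: 9,220 × 0.73 = 6,731; false events: 6,731 × 0.10 = 673
- Genuine events: new diagnoses 0.9 × 420 × 9 = 3,402; untreated earlier-diagnosed men 9,220 × 0.27 = 2,489; total 5,891
- Added: 673 / 5,891 = 11%

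At 1% loss the same steps give 55 / 6,912 = 0.8% and 67 / 5,891 = 1.1%. At 0% loss, treated men add no false events.

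**The case against.** The strongest reply is that the plan already excludes previously treated men. A reader might infer from the missing viral load condition that men already treated and suppressed are counted as new suppressions by rule. The text does not support that. Only men whose earlier treatment is unrecorded, and untreated men who happen to be below 200, can pass.

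A reader might also infer that the incidence of suppression itself is inflated. That goes too far as well: incidence and median time are confined to new diagnoses, and the sample size reasoning for this aim also rests on newly diagnosed men. Nor can it be said that false events occur at time zero. That presumes the clock starts at the first viral load, and the article gives no origin at all for earlier-diagnosed men.

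Covariates states that only sexual behaviour variables are likely to be missing from a substantial number of records. That remark concerns covariates in the extracted records. It gives no assurance about treatment before 2009 or outside the network.

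How treatment history is ascertained could properly be left to a fuller document. The event definition and its entry conditions, however, are fixed in the article, and the gap lies there.

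Finally, setting the false events only against events in new diagnoses gives a larger share: 277 / 4,860 = 6% to 673 / 3,402 = 20%. That leaves out untreated earlier-diagnosed men, whose genuine events belong to the same model.

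**Conclusion.** The concern holds for one secondary analysis: the Cox predictor model in the positive cohort. Outcome 5 does not ensure that earlier-diagnosed men are at risk at entry, and their time origin is undefined. The incidence and median-time estimates in newly diagnosed men are largely unaffected, and the primary aim does not use this outcome.

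The size is illustrative. It is nil for treated men if their history is complete, about 1% added events at 1% record loss, and roughly 4-11% at an assumed 5-10% loss. Taking all treated men as suppressed, and using 2014 coverage for entries from 2009 on, pushes the share up. Counting every untreated earlier-diagnosed man as a genuine event pushes it down. Because false events would cluster in one type of patient, even a modest share could shift the predictor estimates.

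**What to change.** In Outcome 5 and Data analyses:
- **Men diagnosed in the study period:** keep diagnosis as the time origin, with no added viral load condition. Adding one while the clock starts at diagnosis would create event-free time by construction and would drop men treated before any recorded viral load.
- **Men diagnosed earlier:** enter them, and start their clock, at the first in-study viral load of 200 or more with no recorded ART before that date. Use 1000 or more in the sensitivity analysis that takes the higher threshold. Report separately those whose first in-study result is already below the threshold.
- **Sensitivity analysis:** repeat the predictor model in men diagnosed in the study period only, as Outcome 3 does. Unrecorded earlier treatment followed by rebound would still pass the viral load rule.
- **Consistency:** state the same populations in Outcome 5 and in Data analyses.

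The cost is a few sentences and one extra model run, using viral loads already held. The downside is that some untreated, earlier-diagnosed men with low viral load leave the predictor model.

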### Covariates

Covariates considered for this study’s analyses will include patient demographic variables (area of residence, age, indigenous status, country of birth, if Australia’s public health insurance scheme ‘Medicare’ was recorded), clinical information (HIV status, STI diagnoses, CD4 cell count and viral load results, hepatitis B and C co-infection), behavioural information (gender(s) of sexual partner, condom use, injecting drug use, recent sex work, and sexual partner numbers) and service provision - related variables (clinic location - urban vs regional/remote, service type - general practice, sexual health clinic, hospital, community-led service). Additionally, treatment information and treatment type will be used to assess the use of HIV antiretrovirals among the negative cohort as pre- and/or post-exposure prophylaxis (‘PrEP’ and ‘PEP’). The only variables likely to be missing from a substantial number of records relate to sexual risk behaviour. For this information we will draw on records from multiple sources and use a recorded diagnosis of rectal chlamydia and gonorrhoea as a surrogate marker of risk [19]. Not all covariates will be relevant to every analysis.

### Data sources

Routine and de-identified patient data will be extracted from participating service databases, encrypted, and transmitted electronically to a secure server using customised software known as GRHANITE™ [20]. These extractions will provide the data relevant to the co-variate and study outcomes described above. The accuracy of GRHANITE™ has been assessed via internal reliability checks, which showed that the software correctly classified all pathology results as positive or negative, and by comparing extracts with external laboratory data, which found 92–95% concordance [21].

Data quality checks will be conducted biannually and will include a review of testing numbers to identify monthly totals exceeding one standard deviation from the mean. We will also compare data between service types (i.e., laboratory tests recorded at participating health services compared to tests reported by the laboratories relevant to that service) and by comparing the number of HIV and STI diagnoses recorded in patient medical record systems to those reported to the jurisdictional health departments. We will also work with participating sites to compare aggregate outputs produced by their systems internally with those extracted via GRHANITE™.

The GRHANITE™ extraction software de-identifies patient data by performing one-way cryptographic transformation of patient details using a secure hash algorithm. The resultant ‘hashes’ are, therefore, based on patient details but completely anonymous; they are generated before data are transmitted from a health service or laboratory to ensure that potentially identifying details are not extracted from a participating service [21]. Patient hashes are generated using four complex algorithms that combine identifiable patient details (e.g., given and surnames, date of birth) to generate unidentifiable strings of code. Using a combination of one or more of these codes, patients will be linked probabilistically between and within health services and laboratories. Matching patients on four out of four hashes represents the highest quality match or what might be considered near certainty while matching on fewer hashes suggests less certainty. All matches will be assessed by comparing available demographic data between services (e.g., widely disparate ages for one patient between multiple services).

